## Abstract

**Background:**

Interparental violence is both common and harmful and impacts children’s lives directly and indirectly. *Direct effects* refer to affective, behavioral, and cognitive responses to interparental violence and psychosocial adjustment. *Indirect effects* refer to deteriorated parental availability and parent-child interaction. Standard Trauma Focused Cognitive Behavioral Therapy may be insufficient for children traumatized by exposure to interparental violence, given the pervasive impact of interparental violence on the family system. HORIZON is a trauma focused cognitive behavioral therapy based group program with the added component of a preparatory parenting program aimed at improving parental availability; and the added component of parent-child sessions to improve parent-child interaction.

**Methods/design:**

This is a multicenter, multi-informant and multi-method randomized clinical trial study with a 2 by 2 factorial experimental design. Participants (*N* = 100) are children (4–12 years), and their parents, who have been exposed to interparental violence. The main aim of the study is to test the effects of two parental components as an addition to a trauma focused cognitive behavioral based group therapy for reducing children’s symptoms. Primary outcome measures are posttraumatic stress symptoms, and internalizing and externalizing problems in children. The secondary aim of the study is to test the effect of the two added components on adjustment problems in children and to test whether enhanced effects can be explained by changes in children’s responses towards experienced violence, in parental availability, and in quality of parent-child interaction. To address this secondary aim, the main parameters are observational and questionnaire measures of parental availability, parent-child relationship variables, children’s adjustment problems and children’s responses to interparental violence. Data are collected three times: before and after the program and six months later. Both intention-to-treat and completer analyses will be done.

**Discussion:**

The current study will enhance our understanding of the efficacy interparental violence-related parental components added to trauma focused cognitive behavioral group program for children who have been exposed to IPV. It will illuminate mechanisms underlying change by considering multiple dimensions of child responses, parenting variables and identify selection criteria for participation in treatment.

**Trial registration:**

Netherlands Trial Register NTR4015. Registered 4th of June, 2013.

## Background

Interparental violence (IPV) is both common and harmful. At least 12 % of 12–16 year old children are exposed to IPV in The Netherlands [1]. In the United States, 16 % of all children witness IPV at some time during their childhood (2–17 years of age) [2]. In a meta-analysis Evans [3] found a strong association between exposure to IPV and trauma symptoms in children, in addition to small to medium associations between exposure to IPV and internalizing and externalizing problems. These findings emphasize the need for effective interventions for children exposed to IPV. Because IPV involves the whole family system, it affects children’s lives directly and indirectly. Witnessing IPV or being physically involved in IPV may directly affect children’s affective, behavioral and cognitive responses, their psychosocial adjustment and symptoms [4]. IPV may also affect children indirectly [4]. It may lead to deteriorated parenting and parent-child relationships [5], which may mediate the link between IPV and children’s maladjustment on various dimensions. Therefore, treatment for children who have been exposed to IPV should target both direct and indirect effects of IPV.

Trauma Focused-Cognitive Behavioral Therapy (TF-CBT) is a well-established treatment for traumatized children. Although TF-CBT has been found to be effective in reducing post-traumatic stress disorder and depressive symptoms among traumatized children [6], we know little about its effective components and the role of parental involvement [7]. Additionally, the literature suggests that TF-CBT may be less effective for children traumatized by exposure to IPV [8, 9]. One explanation may be that the standard components of TF-CBT have been developed for parents to learn how they can help the child to process traumatic experiences. These components may fail to address the pervasive impact of IPV on parents’ psychological functioning, their parental behavior, and the parent-child relationship [8]. The present study aims to test the relative efficacy of two components added to TF-CBT focussing on parent-related aspects of IPV, namely parenting and parent-child interactions, and thereby provides crucial insight in the mechanisms and mediating effects of treatment on children exposed to IPV. The group-based treatment developed by [name], [name] and [name] in the Netherlands is called HORIZON [10]. In addition to a regular TF-CBT-based treatment, the HORIZON includes two specific components focusing on parents who have let their children to become exposed to IPV. The HORIZON thus consists of three parts, two specific parental components for IPV families and TF-CBT-based child and parent components.

### Direct effects of IPV on children

Being exposed to IPV affects children on a variety of dimensions. Children’s responses are often differentiated in *emotional*, *behavioral*, and *cognitive* responses [11]. To explain these direct effects, Emotional Security Theory [4] and Cognitive Context theory [12] have proposed several mechanisms that mediate the developmental pathways towards psychosocial maladjustment and symptoms, as well as moderating factors that may exacerbate or buffer against the effects of IPV on children.

*Emotional Security Theory* is based on the assumption that children derive a sense of emotional security from their trust in the integrity of the family system. IPV undermines children’s trust, leading them to make efforts to restore it. Although children’s affective, behavioral, and cognitive responses and adaptations toward restoring a level of emotional security may be adaptive in the IPV context, they may be maladaptive in other contexts (e.g., school, peer contacts). This may result in emotional, social, and behavioral maladjustment and problems [13]. To illustrate, Davies et al. [14] and Katz et al. [13] found that children exposed to IPV were less competent in modulating their emotions than children who were not exposed to IPV. This under-developed emotion competence may explain links between IPV and children’s maladjustment [13].

Children’s immediate *behavioral* responses to IPV include approach and avoidance behaviors that serve to regulate exposure to the disturbing affect displayed in marital violence and its aftermath [15, 16]. Avoidance behavior is generally considered as a less adaptive coping strategy to respond to traumatic experiences than approach behavior [17]. To illustrate, Gable [18] found that approach motives and goals in relationships were reliably associated with less loneliness and more relationship satisfaction than avoidance motives. Although not consistently found, both approach and avoidance behaviors in the context of family conflict appear related to children’s symptoms [11].

Children’s *cognitive* responses to violence may shape their beliefs and expectations about aggression, about close relationships and about themselves. They might start to believe that aggressive behavior is an acceptable way of problem solving [19]. Children exposed to IPV and other forms of violence may come to value aggression more positively than other children [20, 21]. Additionally, Grych’s Cognitive Context theory suggests that children may blame themselves for what happened or believe they are powerless to cope with IPV [22]. Finally, children may become more vigilant to threat-related cues in the environment [23]. These beliefs and expectations may influence their behavior in peer-relationships, in family-relationships and in romantic relationships [22]. Each of these cognitive responses of children can be assumed to exacerbate children’s psychosocial maladjustment in response to IPV.

Components of TF-CBT such as emotion regulation, cognitive reprocessing, psycho-education and skill building have been shown to reduce internalizing problems, externalizing problems, and trauma symptoms [9, 24]. Nevertheless, to our knowledge research has not yet explicitly addressed whether TF-CBT or TF-CBT-based interventions ameliorates children’s symptoms by improving children’s emotion regulation. Furthermore, TF-CBT was found to reduce trauma-related avoidance behavior in children exposed to IPV [9]. Whether children’s approach behavior changes after TF-CBT or TF-CBT-based interventions is currently unknown. Also, the cognitive component of TF-CBT explores and corrects children’s harmful attributions about the cause of, responsibility for, and results of traumatic experiences such as family violence [17, 25]. Whether cognitive responses change after TF-CBT among children who have been exposed to IPV has not yet been examined. The present study examines how these emotional, behavioral, and cognitive responses change over the course of treatment and how these changes affect treatment outcomes and children’s psychosocial adjustment.

### Indirect effects of IPV on children

Being exposed to IPV also affects children indirectly. Not only children, but parents are likely to be traumatized as well [26]. Parents experience a broad range of emotional, cognitive and behavioral consequences of IPV. These responses can be assumed to affect their parenting and the parent-child relationship. The *Spillover hypothesis* emphasizes that distressing experiences in the interparental relationship, such as IPV, carry over to parenting behavior [27] and to the parent-child interaction (e.g., [28]). We propose two mechanisms that may explain how the experience of IPV may affect parenting, a cognitive-emotional mechanism and a behavioral mechanism. In the following, we will describe these theoretical underpinnings of the two specific parental components of the HORIZON.

### Cognitive-emotional mechanism: parental availability

Mothers who have been part of IPV tend to underestimate the extent to which their child has been exposed to and is affected by the IPV [29, 30]. This underestimation is assumed to be partly due to the fact that mothers may focus their attention on themselves and their own traumatic experience rather than on their children’s traumatic experience [29, 30], and to the fact that their children’s behavior is a reminder of their own trauma which triggers avoidance e.g. [31]. Also, mothers who have experienced traumas, such as IPV or childhood abuse, showed difficulties in adopting an open, non-defensive style of communication when talking about emotions with their children [32]. Additionally, they appeared less child-centered and less available to their children [33]. Moreover, IPV has been linked to parenting styles that are characterized by emotional unavailability and psychological control e.g., [34, 35]. Thus, parents from violent families may be so absorbed by their own problems that they are less likely to take their children’s perspective and to show insight in their children’s developmental needs, behavior, and motives [36]. This deteriorated insightfulness may partly explain why children traumatized by exposure to IPV benefit less from TF-CBT than children who were traumatized by experiences that did not have a traumatic impact on their parents at the same time [8, 9].

For children to feel secure and supported by their parents, parents need to be sensitive to their children’s needs, accurately recognize their children’s signals, and appropriately respond to these signals [37, 38]. Similarly, for children to benefit from a trauma-focused treatment, such as TF-CBT, parental involvement to support the child is necessary [39]. Accordingly, increasing parents’ cognitive and emotional availability to the child should be a primary focus of treatment for children exposed to IPV. To this end, [name], [name], and [name] developed a preparatory program for parents exposed to IPV [10]. This preparatory program was aimed to increase parental availability and insightfulness in their children’s needs. Parents are coached to enhance reading their children’s behavioral and emotional signals and to adequately interpret these signals in light of the child’s age, the development, and type of IPV the child has been exposed to. The preparatory program component precedes the TF-CBT-based treatment.

### Behavioral mechanism: parent-child interaction

Parents who have experienced and have been exposed to IPV tend to engage in ineffective parenting. Compared to non-exposed parents they used more negative and less positive parenting, are likely to use more harsh discipline towards their children [40], showed more aggression in the parent-child relationship [41], and were less supportive and less effective [42]. Buehler and Gerard [5] found that ineffective parenting mediated the link between marital conflict and children’s maladjustment. In their study, ineffective parenting comprised of harsh discipline (e.g., spanking), low involvement (e.g., talking and reading with child), and reduced parental presence (i.e., time spent together). These findings suggest that IPV reduces parents’ capacity to support their child, to interact with him/her in a safe and comforting manner, and to be available to fulfill and sensitively respond to his emotional and cognitive needs [43].

To optimally benefit from trauma-focused treatment, parental support is important for children [39]. Accordingly, we propose that trauma-focused treatment for children exposed to IPV can be enhanced by improving parents’ emotional support and parent-child interaction. To this end, [name] et al. [10] developed the second specific parental component, the parent-child interaction sessions, to complement the TF-CBT-based treatment. These weekly sessions follow the child and parent TF-CBT-based treatment sessions. They aim to help parents to gain new insights in their children’s functioning and to more accurately and positively respond to their child’s emotions and behaviors by interacting with their child.

### Trial objectives

In the present project, we will examine the efficacy of the two parental components of the HORIZON, the preparatory program for parents and the parent-child interaction sessions. HORIZON is a TF-CBT-based group treatment for children exposed to IPV. For a complete description of the treatment in Dutch see [10, 44], and for a summary see paragraph ‘Intervention’. In a randomized-controlled design, we will add the parental components to a TF-CBT-based core treatment to examine their independent and combined effects on parents’ and children’s outcomes. Overall, we expect both parental components to add to the efficacy of the TF-CBT-based core treatment. Specifically, we expect that, as compared to parents who did not participate in the preparatory program, parents who participated in the preparatory program show a greater increase in parental availability. In the same vein, we expect that the parents who participated in the parent-child interaction sessions show a greater increase in effective and positive parenting and a greater decrease in negative parenting than parents who did not participate in these sessions. These effects of the parental components should contribute to parents’ and children’s outcomes and reduction of symptoms.

### Primary objectives

The primary objective of the present study is to examine the efficacy of two parental components that complement a TF-CBT-based core treatment for children who have been exposed to IPV. Specifically, the study involves a randomized controlled trial with a 2 (parent preparatory program present vs. absent) X 2 (parent-child interaction sessions present vs. absent) factorial design to evaluate the effects of these two parental treatment components on child symptoms.

### Secondary objectives

Our second goal is to evaluate the effects of these two parental treatment components on child adjustment. Our third goal is to investigate mechanisms underlying the efficacy of treatment for children who have been exposed to IPV by examining associations between: child symptoms, on the one hand, and, 1) child responses (i.e., child emotional, behavioral, and cognitive responses, 2) parental availability and 3) parent-child interaction, on the other.

Our fourth goal is to examine specific hypotheses of change. Specifically, we will test whether, as predicted, the preparatory program leads to increased parental availability and whether the parent-child interaction sessions lead to improved parenting behavior. Also, we will explore whether these changes lead to a reduction in symptoms.

To ensure comparability of the randomized conditions, we will control for duration and severity of the IPV [45], parental psychopathology [46], and new incidents of IPV.

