### Randomization, blinding, and treatment allocation

Recruitment will take place in three mental health centers in The Netherlands. For each center families are referred for treatment after children have been exposed to interparental violence. As soon as a group of approximately 8 families have met the inclusion criteria for participation in the HORIZON group treatment (see Inclusion and Exclusion Criteria), and after informed consent is obtained, the families participating in the study will participate in T1 measurements. Parents and children are asked to fill out questionnaires and to participate in two observational tasks. Additionally, the parent is interviewed about the observational tasks. After T1, the group will be randomly assigned to one of the four treatment conditions (see Fig. 1) by an independent researcher using a randomization procedure with lottery drawings. Conditions 1 & 2 will start one week after T1, and conditions 3 & 4 will start seven weeks after T1. One week (T2) and six months (T3) after the end of the program, parents and children are again invited to fill out questionnaires (see Fig. 2). At all assessments the teacher is also sent a questionnaire. Typically, the intervention group consists of two child groups (4–7 years and 8–12 years, respectively) and one parent group. Usually there is only one parent group, because families often have more than one child who participate in the intervention, and because parents without visitation rights do not participate. The child groups receive treatment at the same time but in different rooms. The parents of children in both groups receive group sessions on the same time. Because it is not feasible for participating trauma centers to start four interventions at the same time, we cannot randomly assign individual children or parents to one of the four conditions. Therefore, we choose randomization by group just before the start of the group therapy and after T1. Parents and children are blind to treatment condition until randomization is carried out just before the (preparatory) program starts. Clinicians will be blind for treatment condition until all families are indicated for treatment. The assessments include videotaped observational tasks. Independent research assistants will code these videos. All coders are blind for treatment condition. Sometimes it will take a few months before families can participate in one of the four group interventions, due to waiting lists and enrollment numbers to form treatment groups. If necessary, parents and children will receive family or individual stabilization intervention during this time. Independent of their experiences with treatment preceding participation in the HORIZON, all participating families will be measured at T1 at the same time to ensure comparability of the families in the study.

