## Measures

### Primary outcome measures

#### Child symptoms

##### Trauma symptoms

*Trauma Symptom Checklist for Younger Children* [50]. The TSCYC is a parent-reported questionnaire for children (3–12 years) measuring posttraumatic stress symptoms on a 4-point Likert scale, ranging from ‘not at all’ (1) to ‘very often’ (4). It consists of 90 items and 11 scales: two scales to assess the validity of the parent’s answers (response level and atypical response), eight clinical scales (anxiety, depression, aggression, PTSS-intrusion, PTSS-avoidance, PTSS-arousal, dissociation and sexual concerns) and a total PTSS score. This total score will be used in analyses. This clinical total PTS scale showed good reliability within a sample of maltreated children in the United States (Cronbach’s α = 0.81–0.91) and in the Netherlands (Cronbach’s α = 0.79–0.91) [51].

*Trauma Symptom Checklist for Children* [52]; Dutch translation: *Trauma Symptoom Controle Lijst voor Kinderen* [53]. This is a questionnaire to assess self-reported posttraumatic stress symptoms at children (8–12 years). It consists of 54 items clustering in 8 scales: two validity scales (underresponse, hyperresponse) and six clinical scales (anxiety, depression, post-traumatic stress disorder, dissociation, anger and sexual concerns). The response categories are the same as in the Trauma Symptom Checklist for Younger Children and reliability was high for the clinical total PTS score, with a Cronbach alpha’s ranging from 0.78 to 0.86 in a sample of sexually abused children [50]. In a sample of maltreated children in the United States the Trauma Symptom Checklist for Children showed discriminant and convergent validity with the Trauma Symptom Checklist for Younger Children [54], and in the Netherlands the Trauma Symptom Checklist for Children showed convergent and criterion validity with other behavioral questionnaires (CBCL, TRF, YSR, CDI) [55].

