#### Internalizing and externalizing symptoms

*Child Behavior Checklist* [56] measures competencies and problem behaviors of children aged 1½ to 18 years. The CBCL has a parent-report and a teacher-report (TRF) questionnaire for 1½–5 years and 6–18 years. The questionnaire measures internalizing (i.e., anxious, depressive, and over-controlled) and externalizing behavior problems (i.e., aggressive, hyperactive, noncompliant, and under-controlled) over the past 6 months. The behavior problems are measured with 120 items on a 3-point Likert scale, consisting of ‘not true’(0), ‘sometimes true’(1) and ‘very/often true’(2). Cronbach alpha’s for the broadband scales in a Dutch sample ranged from 0.78 to 0.93 for the CBCL [57] and from 0.86 to 0.96 for the TRF [58].

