### Statistical analyses and sample size calculation

All variables are measured on at least an ordinal scale. All scale scores will be examined for normality. Should we observe deviations, steps will be taken to ensure optimal estimation of parameters in our analyses. The proposed study includes a nested structure, because individuals are treated within groups. Following the recommendations by Peugh [118], we will calculate design effects to assess group-level dependency and examine whether multi-level modeling is required. To ensure comparability of the randomized conditions, we will control for duration and severity of the IPV [45], parental psychopathology [46], and new incidents of IPV. Power calculations were performed using the program G*power 3 [119], assuming that individual-level effects can be treated as independent data. We determine required sample size to be 100 parent-child dyads, achieving statistical power of at least .80 for the primary and secondary objectives, as described in more detail in the following paragraphs. We will test for the randomness of missing data. If this is the case we will use multiple imputation.

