### Primary objective

The first goal of the present study is to examine the efficacy of two parental components that complement a TF-CBT-based core treatment for children who have been exposed to IPV. Therefore, a multiple regression analysis will be executed with two dummy variables as independent variables, representing both parental components (dummy 1 = parent preparatory program present vs. absent; dummy 2 = parent-child interaction sessions present vs. absent) and their interaction. Dependent variables are child symptoms (primary outcomes) at the three time points (T1, T2, and T3) clustered into 1) Trauma symptoms, 2) Internalizing symptoms, 3) Externalizing symptoms. Analyses will be independently executed for the three dependent variables. Because children in each group receive intervention, a medium effect size is expected (f^2^ = .15). With a maximum of five predictors and an alpha of .05, we achieve a power of .84 with 100 children included in the study.

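### Child age is missing from the covariates meant to make the conditions comparable, a modest and avoidable loss of precision in a trial of 4- to 12-year-olds randomised by whole group

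*Protocol article*

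**What the plan says.** The covariates are named twice in the protocol article, with the same purpose each time. Secondary objectives (under Trial objectives) states that "we will control for duration and severity of the IPV [45], parental psychopathology [46], and new incidents of IPV". Statistical analyses and sample size calculation repeats the list: "To ensure comparability of the randomized conditions, we will control for duration and severity of the IPV", again followed by parental psychopathology and new incidents.

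Under Primary objective in the statistics section, "a multiple regression analysis will be executed with two dummy variables as independent variables, representing both parental components", together with their interaction. The outcomes are trauma, internalizing and externalizing symptoms: "Dependent variables are child symptoms (primary outcomes) at the three time points (T1, T2, and T3"). Power of .84 is stated for 100 children, f² = .15, alpha .05 and at most five predictors. Child age is in neither the covariate list nor the model.

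Age matters in three other places:

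- Randomization, blinding, and treatment allocation: "Typically, the intervention group consists of two child groups (4–7 years and 8–12 years, respectively) and one parent group". Whole groups of about 8 families are assigned by lottery, and no stratification by age is described.
- Trauma symptoms, on the TSCC: "This is a questionnaire to assess self-reported posttraumatic stress symptoms at children (8–12 years"). The parent-reported TSCYC covers ages 3 to 12.
- Internalizing and externalizing symptoms: "The CBCL has a parent-report and a teacher-report (TRF) questionnaire for 1½–5 years and 6–18 years".

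**The concern.** A list whose declared purpose is comparability leaves out the characteristic by which the trial itself usually divides the children for treatment. Age is known for every child before randomisation. It can plausibly shift symptom levels across a 4-to-12 range, and it decides which instruments a child completes. By contrast, the list includes new IPV incidents, which can occur after randomisation.

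Because few whole groups are randomised, the share of younger children can differ by chance between the levels of a factor. Without an age term, that difference moves the estimated component effect in the one allocation actually drawn, and age variance stays in the residual. Adding age after outcomes are seen would be a data-dependent choice, so the time to name it is now.

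**Working it through.** **1. The plan's own figure.** Overall F test of a regression: λ = f²·N = 0.15 × 100 = 15, df = 5 and 100 − 5 − 1 = 94. Power is 0.843, so the stated .84 reproduces. Age plays no part in it.

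**2. Predictor count.** Two dummies and an interaction make 3 terms. Duration, severity, parental psychopathology and new incidents, at one term each, make 4. The total is 7, or 6 if duration and severity form one score; both exceed five. For the overall model test at f² = 0.15 and N = 100, power is:

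| Predictors | Power |
|---|---|
| 5 | 0.843 |
| 6 | 0.813 |
| 7 | 0.785 |
| 8 (age added to 7) | 0.758 |

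This fall belongs to the overall model test. For a test of the 3 component terms alone at f² = 0.15, power is 0.904 with 7 predictors in the model and 0.904 with 8. A useless age term would therefore cost the component tests essentially nothing.

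**3. Gain from adjusting for age.** The article gives no age-outcome association, so R², the share of the remaining outcome variance explained by age, is an assumption (0 to 0.15). Children are treated as independent, as in the article's own power calculation.

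- The standard error is multiplied by √(1 − R²).
- For one component, compared 50 v 50 at d = 0.5: f² = d²/4 = 0.0625 without age, and 0.0625/(1 − R²) with age.
- df = 1 and 92 without age, 1 and 91 with age.

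| R² of age | SE falls by | Power, one component (0.696 without age) | Power, 3 component terms (0.904 without age) |
|---|---|---|---|
| 0 | 0% | 0.696 | 0.904 |
| 0.02 | 1% | 0.705 | 0.910 |
| 0.05 | 2.5% | 0.718 | 0.919 |
| 0.10 | 5% | 0.741 | 0.934 |
| 0.15 | 8% | 0.765 | 0.947 |

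To put R² on a scale: with half the children in each age group and a gap of a SD between them, R² = 0.25a²/(1 + 0.25a²). Gaps of 0.3, 0.5 and 0.7 SD give 0.022, 0.059 and 0.109.

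**4. Chance imbalance.** The number of groups is not given. The article speaks of about 8 families per group and says that families often bring more than one child. Two layouts were assumed: 12 groups of 8 children and 8 groups of 12, each with half the groups at each level of a factor.

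- *Evenly mixed groups* (each child equally likely to be younger or older), 12 groups of 8: the SD of the difference in age shares is √(2 × 0.25/48) = 0.10. Simulation with 20,000 draws agrees, and 95% of draws lie within 0.21.
- *Unevenly mixed groups* (share varying between groups with SD 0.2), 8 groups of 12: the SD is 0.17, and 95% of draws lie within 0.33.

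The shift in an unadjusted component effect is the imbalance times the age gap. At the 95% limits this runs from 0.21 × 0.3 = 0.06 SD to 0.33 × 0.7 = 0.23 SD.

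**The case against.** The strongest reply is that nothing here is an error. The article does not say that no other covariate will be used, and a condensed article may leave the final adjustment set to an analysis plan. That would carry more weight if the article were silent. It names a specific list twice, with a purpose, so a one-term change to that list is a fair request.

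A second reply is that groups are randomised and usually contain both age bands, so age is crossed with condition. This stands. A reader might infer that the component effects are biased, and the documents do not support that. The loss is precision. Chance imbalance lies within the ordinary error rate if clustering is handled, and the article plans to examine design effects.

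A third reply is that T1 scores already carry the age differences. This stands in part. If T1 enters as a covariate, much of the stable age variance goes with it. But the article lists T1 among the dependent variables and does not name it as a covariate.

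Other strong readings also fail:

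- *Every group is split by age.* The article says this is typical, not universal.
- *The informant changes with age for all primary outcomes.* Only the TSCC is limited by age. The TSCYC is one parent form for the whole range, and the CBCL/TRF has parent and teacher report at both ages.
- *An age term repairs the change of form.* The CBCL/TRF break lies between 5 and 6 and the treatment split between 7 and 8. No covariate makes different forms commensurable; that needs a scoring rule.
- *Earlier stabilisation treatment belongs in the model too.* The article says "If necessary, parents and children will receive family or individual stabilization intervention during this time", but this precedes T1 and randomisation. The documents name no data source for such a covariate and give no basis for its size.

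**Conclusion.** The point holds as a modest recommendation on precision. Age is absent from a list meant to secure comparability and from the primary model, in a design where age structures both treatment and measurement and few units are randomised. It overturns no stated figure.

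If age explains 0 to 15% of outcome variance, adjustment lowers the standard error by about 0 to 8% and adds 0 to 7 points of power for one component at d = 0.5. Under the assumed layouts and an age gap of 0.3 to 0.7 SD, chance imbalance at its 95% limit shifts an unadjusted effect by 0.06 to 0.23 SD. All of these figures rest on assumed age-outcome associations, and the imbalance figures also on assumed group numbers. If T1 is adjusted for or scores are age-normed, the gain is near the low end. The case for the change rests on its negligible cost if age proves irrelevant, more than on a large expected gain.

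**What to change.** In Secondary objectives (under Trial objectives), Statistical analyses and sample size calculation, and Primary objective, add the child's age at T1, in years, as a fixed baseline covariate in every component model. Age in years is preferable to a 4–7 v 8–12 indicator, because that cut does not match the CBCL/TRF break.

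In the same edit, revise the limit of five predictors. List every term in the model, say whether the power refers to the overall model or to the component terms, and restate it.

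The cost is one sentence on the covariate, a corrected power statement and one degree of freedom. Age is already known for every child, so no new data are needed.
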